### Recruitment of participants

Trial participation is invited through public antenatal clinics, antenatal education classes and on the Birth Suites at both recruiting hospitals. Although both sites use a number of models of care in the provision of maternity services, all women return to the public antenatal clinic at a particular gestation; 36 weeks and 30 weeks at the Site One and Site Two, respectively. At this time women will be provided with information regarding the trial. The recruitment strategy aims to provide information regarding the trial prior to presentation to the Birth Suite in labour.

### Consent

The recruitment strategies are designed to ensure that women receive information regarding SWI as an intervention for back pain and information on the trial, at or before 36 weeks gestation (i.e. prior to inclusion criteria of 37-42 weeks gestation). The majority of women will consent to the trial on presentation to the Birth Suite in labour at both sites. Clinical midwives and/or clinical facilitators from both sites will be available to receive informed consent. A trial investigator will be available via mobile phone to provide support for midwives undertaking consent and enrolment procedures, and to promote continuity of procedures and trial fidelity across the two sites. Women who have been provided with a participant information sheet and indicate an interest in joining the trial will be able to contact the research midwife or investigators for further information or clarification before consent. A video demonstrating the four injection technique is available for women to access at the trial website. http://maternity.mater.org.au/switch. A form will be placed with the woman's chart to highlight that the woman has consented to participate in the study if eligibility criteria is met. Verbal consent will be re-affirmed immediately prior to randomisation and documented within in the woman's clinical chart. Women are able to withdraw consent at any time (i.e. before, during or after the procedure and/or before completing follow-up questionnaire) without affecting their usual clinical care or request alternative and available means of analgesia.

### Randomisation

The randomisation schedule for Site One will be prepared by a statistician using a computer-generated list of random numbers. Blinding of allocation to the study intervention will be undertaken using opaque sealed envelopes prepared by Site One administrative staff. A separate randomisation sequence was generated for Site Two in permuted blocks of four to ensure an equal number of participants across both arms of the trial where smaller recruitment numbers are expected. Blinded allocation at this site will be undertaken using similarly prepared opaque sealed envelopes (Figure 3).

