### Exclusion criteria

Gestation <37 weeks

Multiple pregnancy

Malpresentation (Breech Transverse etc.)

Second stage labour

Pharmacological analgesia prior to SWI

Back pain assessed by VAS <7

Women whose labour would be considered high risk.

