### Blinding

At both sites, the envelopes will be kept in a locked cupboard on the birth suite and available for randomisation 24 hours/day. The key will be held by the Midwifery Team Leader who will obtain and open one envelope, then with the assistance of another midwife will administer the SWI using the technique detailed within the envelope. The two midwives will be present during the procedure regardless of the SWI technique being administered, to assist with blinding of the procedure to the midwife providing care and collecting data. The injection site(s) will be covered with a hypoallergenic opaque dressing to prevent visualisation of the number of injections used. The participants will be aware not to discuss the type of intervention they were allocated to with their midwife. The midwife caring for the woman will then return to collect the intervention data.

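### Site Two's single, published block length of four lets anyone who follows the sequence deduce one third of its allocations, which weakens concealment there

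*Protocol article*

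**What the plan says.** All references are to the protocol article.

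- **Randomisation.** Site One has a computer-generated list with no blocking stated. Site Two has a sequence of its own, drawn up "in permuted blocks of four to ensure an equal number of participants across both arms of the trial". The reason given for seeking that balance is that this is the site "where smaller recruitment numbers are expected". Concealment relies on envelopes: "Blinded allocation at this site will be undertaken using similarly prepared opaque sealed envelopes". No further stratification is described, so Site Two has one sequence to follow.
- **Blinding.** The envelopes are locked up on the birth suite at each site. The Midwifery Team Leader holds the key and is the person "who will obtain and open one envelope, then with the assistance of another midwife will administer the SWI". These two staff therefore see the allocation. The midwife who cares for the woman and records the data is kept masked by having two midwives present for either technique, by an opaque dressing, and by asking women not to discuss their allocation with her.
- **Consent.** "Clinical midwives and/or clinical facilitators from both sites will be available to receive informed consent". Most women consent on arrival at the birth suite in labour, and verbal consent is confirmed again just before randomisation. The section does not say that these staff are distinct from those who open envelopes.

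**The concern.** Opaque envelopes hide the card inside them. They do not hide what the pattern of earlier cards reveals. With a constant block of four in a 1:1 trial, the last place in every block is fixed by the first three, and the third place is sometimes fixed by the first two. In this open-label procedure, staff on the ward learn each allocation as it happens, and the block length is in the published article.

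Concealment matters at the moment of enrolment. If someone who can influence whether or when a woman is enrolled knows which technique comes next, the arms can come to differ in the kind of women they contain. Selection of that sort cannot be reliably undone in the analysis. The primary outcome is self-reported pain compared with a 1 cm margin, so the comparison depends on the two arms being alike at entry.

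**Working it through.** The article gives no predictability figure, so there is none to reproduce. The result depends on the block scheme alone and not on the sample size.

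**Inputs**
- Block length 4, constant (Randomisation).
- Ratio 1:1, hence two places per arm in each block (Randomisation, from the aim of equal numbers).
- Assumption about the observer, not stated in the article: he or she knows the block length, knows where each block starts, and has seen every earlier allocation in the current block.

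**Step 1: certain allocations.** Write S for the single and F for the four injection technique. The six equally likely orders are SSFF, FFSS, SFSF, SFFS, FSSF and FSFS. An allocation is certain once the other arm's two places are used.
- SSFF and FFSS (2 of 6 orders): places 3 and 4 are certain.
- The other 4 of 6 orders: only place 4 is certain.
- Total: 2 × 2 + 4 × 1 = 8 certain places out of 6 × 4 = 24, or 33.3%.
- By place: 0, 0, 1/3, 1.

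**Step 2: correct guesses.** The observer always guesses the arm with more places left.
- Place 1: 1/2.
- Place 2: 2/3 (two of the three remaining places belong to the other arm).
- Place 3: 1/3 × 1 + 2/3 × 1/2 = 2/3.
- Place 4: 1.
- Mean: (1/2 + 2/3 + 2/3 + 1)/4 = 17/24 = 70.8%, against 50% with no information.

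**Step 3: alternatives.** Fixed blocks of 6 and 8 were enumerated in the same way. The mixed schemes were simulated (1,500 sequences of 60 allocations). There the observer sees every allocation and knows the set of possible sizes, but not which size each block has.

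| Scheme | Certain | Guessed correctly |
|---|---|---|
| Fixed 4 (plan) | 33.3% | 70.8% |
| Fixed 6 | 25% | 68.3% |
| Fixed 8 | 20% | 66.6% |
| Random mix of 4 and 6 | about 5.5% | about 69% |
| Random mix of 4, 6 and 8 | about 2% | about 68% |

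Varying the block size removes nearly all the certainty. It lowers the best-guess rate by only about 3 percentage points.

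**Step 4: price in balance.** The largest imbalance within a block is half its length: 4/2 = 2 women now, and 8/2 = 4 women if blocks of eight are included.

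**The case against.** The case against is substantial, and most of it limits how far the point reaches.

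- **Recalling the last few women is not enough.** Two identical allocations in a row may straddle a block boundary and then prove nothing. The observer needs the boundary and all earlier allocations in the block. Envelopes are available around the clock, so one person is unlikely to see every opening. This stands: one third is the share open to a full tracker. The article neither ensures nor prevents such tracking.
- **A reader might infer that the people who enrol are the people who know the allocations.** The article does not say so. It deliberately keeps the caring midwife masked, and it does not give consent or eligibility decisions to the team leader or assistant. Overlap is possible and is not excluded; that is all that can be said.
- **A reader might infer that entry criteria are open to manipulation.** The VAS threshold rests on the woman's own rating, so it is not a staff judgement. The exclusion "Women whose labour would be considered high risk" leaves some discretion, but no section assigns it to the envelope opener.
- **A reader might infer that envelopes are unnumbered or opened out of order.** The article is silent. A condensed article commonly leaves such procedure to the full protocol, and the participant-flow figure is not shown. No finding follows.
- **A reader might infer a false claim of non-inferiority.** That needs Site Two's share of recruitment, the strength of any steering and its direction, none of which is given. Purely as an illustration, suppose shares of 10%, 25% or 40% and a 1 cm difference created among all deducible allocations. The shift is then share × 1/3 × 1 cm, or 0.03, 0.08 or 0.13 cm, against a 1 cm margin. It could run either way.
- **Blocking has a stated purpose.** Balance at a small site is a sound reason for short blocks. It is not a reason for a constant, disclosed length.

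**Conclusion.** The point holds as a modest weakness in a stated design choice, at the smaller site only. The one-third and 70.8% figures are exact for an observer who knows the block length and boundary and has followed the block. For anyone who sees only some allocations, the share is lower. The masking of the caring midwife protects outcome recording for the current woman; it does not prevent prediction of the next allocation by staff who open envelopes. The article does not show that steering is likely, and it gives no basis for stating how large a bias would be or which technique it would favour. The case for a change is that the weakness is avoidable at very little cost.

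**What to change.** For the Site Two envelopes not yet opened, have the statistician prepare a new site-specific list with block sizes varying at random, for example 4, 6 and 8. Withhold the sizes from ward staff and from any publication until recruitment ends. The existing Site Two list is no obstacle, since unopened envelopes can be replaced.

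The cost is one new list and one new set of envelopes at the smaller site, plus the wider possible imbalance shown above. No additional participants or staff are needed. The change should be described as removing near-certain foreknowledge, not as making the sequence unguessable.

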**Figure 3 F3:**
[figure not shown]
**Randomisation and participant flow**.

### Blinding

At both sites, the envelopes will be kept in a locked cupboard on the birth suite and available for randomisation 24 hours/day. The key will be held by the Midwifery Team Leader who will obtain and open one envelope, then with the assistance of another midwife will administer the SWI using the technique detailed within the envelope. The two midwives will be present during the procedure regardless of the SWI technique being administered, to assist with blinding of the procedure to the midwife providing care and collecting data. The injection site(s) will be covered with a hypoallergenic opaque dressing to prevent visualisation of the number of injections used. The participants will be aware not to discuss the type of intervention they were allocated to with their midwife. The midwife caring for the woman will then return to collect the intervention data.

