### Interventions

#### Control group

Participants randomised to the control group will be given SWI using the standard four injection intradermal technique into the skin surrounding the Michaelis rhomboid over the sacral area. Anatomically, the injections will be administered: two over each posterior superior iliac spine (PSIS) and two three cm below and one cm medial to the PSIS (Figure 1). Minor discrepancies or changes to the anatomical position or alignment of the four injections have not been shown to impact on any analgesic effect [18].

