#### Intervention group

Participants randomised to the intervention group will be given SWI using the single injection intradermal technique.

The anatomical site for the single injection will be over the single most painful point as indicated by the woman (Figure 2).

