
**Figure 4 F4:**
[figure not shown]
**Possible scenarios of observed treatment differences [adapted from **[22]**]**. Shaded area indicates non-inferiority margin.

In the event that women experience no relief from the single injection and request the four injection technique, these women will remain within the study, and the data will be analysed according to ITT and per protocol principles.

Women requesting a repeat injection will receive the standard four injection technique. A pre-injection VAS score will be sought prior to administration and post injection VAS score will be collected at 30 minutes. These will be reported separately.

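### Blinding of the midwife who collects the VAS scores is not secured as written: no common dressing is specified, and the plan foresees a request that would reveal the arm

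*Protocol article*

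**What the plan says.** All references are to the protocol article.

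- **Blinding.** The person to be blinded is the midwife who cares for the woman and records the data. Four measures are described. Two other midwives attend in both arms: "The two midwives will be present during the procedure regardless of the SWI technique being administered", and this is "to assist with blinding of the procedure to the midwife providing care and collecting data". The dressing: "The injection site(s) will be covered with a hypoallergenic opaque dressing to prevent visualisation of the number of injections used". Non-disclosure by the woman: "The participants will be aware not to discuss the type of intervention they were allocated to with their midwife". The caring midwife comes back after the procedure: "The midwife caring for the woman will then return to collect the intervention data".
- **Control group.** The injections go to "two over each posterior superior iliac spine (PSIS) and two three cm below and one cm medial to the PSIS".
- **Intervention group.** The one injection is placed "over the single most painful point as indicated by the woman".
- **Data collection.** The caring midwife records the VAS at baseline, at 10 minutes and at 30-minute intervals to two hours. The 30-minute score supplies the primary outcome.
- **Statistical analysis, text after Figure 4.** "In the event that women experience no relief from the single injection and request the four injection technique", they stay in the study and are analysed by both ITT and per protocol principles. The next paragraph says that women who ask for a repeat injection receive the four injection technique, and it names no arm.

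**The concern.** The dressing is meant to hide how many injections were given, but it is defined by where they were given. A cover that follows the injected sites is bilateral and extends below the iliac spines in one arm. In the other it sits over a single point that varies between women. Opacity hides the marks on the skin but not the place or size of the cover. The caring midwife attends a woman with back pain for up to two hours of scoring and may well see it.

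The second weakness is the request foreseen after Figure 4. A woman who asks for the four injection technique because the single one did not help has said which arm she is in. Only single-injection women can make that request in those terms, and only those without relief would. If it reaches the data collector, unblinding depends on both arm and response. This sits badly with the instruction not to discuss allocation.

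At stake is the neutrality of the person who presents the scale and records the score in a non-inferiority comparison with a 1 cm margin.

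**Working it through.** **Step 1. The passages side by side.**

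| Feature | Four injections | Single injection | Common to both arms as written? |
|---|---|---|---|
| Number of sites | 4 | 1 | No |
| Location | Fixed, bilateral | Chosen by the woman | No |
| Dressing | Over the injected sites | Over the injected site | Opaque in both; common size and position not stated |
| Staff at the procedure | Two midwives | Two midwives | Yes |
| Caring midwife returns afterwards | Yes | Yes | Yes |
| Request foreseen after no relief, naming the other technique | No | Yes | No |
| Plain request for a repeat | Four injections given | Four injections given | Yes |

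The two staffing rows protect the procedure itself. The dressing and the woman's silence have to protect the period afterwards, when the scores are taken. The last row matters for the remedy: a plain request for a repeat leads to the same technique in both arms and so reveals nothing. Only naming the technique does.

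**Step 2. Reproduce the plan's sample size.** Inputs from Sample size: margin 1 cm, SD 2.5 cm, true difference 0, one-sided alpha 0.025, power 90%. With the non-central t distribution, 132 per group gives power 0.8993 and 133 gives 0.9015. The stated 133 per group is therefore the smallest size that reaches 90%.

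**Step 3. Standard error of the difference.**

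SE = SD × √(2/n) = 2.5 × √(2/133) = 0.307 cm

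**Step 4. Sensitivity to a shift in recorded scores.** The article gives no figure for such a shift, so b = 0.1, 0.2 and 0.3 cm are assumptions.

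- Shift toward the single injection, with the true difference at the 1 cm margin: type I error ≈ 1 − Φ(1.96 − b/SE).
- Shift against the single injection, with a true difference of 0: power is that of the t-test with non-centrality (1 − b)/SE on 264 degrees of freedom.

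| b (cm) | b/SE | Type I error, normal formula | Type I error, non-central t | (1 − b)/SE | Power, non-central t |
|---|---|---|---|---|---|
| 0 | 0 | 0.025 | 0.025 | 3.262 | 0.901 |
| 0.1 | 0.326 | 0.051 | 0.051 | 2.936 | 0.833 |
| 0.2 | 0.652 | 0.096 | 0.095 | 2.610 | 0.739 |
| 0.3 | 0.979 | 0.163 | 0.162 | 2.283 | 0.624 |

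These figures show how sensitive the test is to any shift of that size, whatever its cause. They do not estimate the effect of the dressing or of the request.

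**The case against.** **One dressing may be intended.** The sentence speaks of a dressing in the singular and gives its purpose. One large sacral dressing, the same in both arms, would satisfy it, and a condensed article may leave the size to the full protocol. This stands against any claim that the blinding fails. A reader might infer that the dressing reveals the arm in every woman, but the text does not say that dressings differ. What remains is that a small patch over one point satisfies the sentence equally well, and the article ties the cover to the sites.

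**The request is an analysis contingency.** The sentence after Figure 4 says how data from such women are handled. It does not tell anyone to name a technique. A reader might infer that the woman has to ask the caring midwife, or that this happens before the 30-minute score. The article states neither the person asked nor the timing. The Background describes relief as almost immediate, so an early request is possible, but it is not documented. The two sections are therefore in tension, not in outright contradiction.

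**Other safeguards exist.** Two midwives in both arms and the caring midwife's absence during the injections are real protections. They do not cover the two hours that follow.

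**The woman is the more direct route.** The VAS is her own rating, she is not stated to be blinded, and the non-disclosure instruction presupposes that she knows her allocation. An identical dressing would leave that untouched. This stands, and it makes the collector's unblinding secondary. The postnatal questionnaire is already given by a blinded researcher.

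**The shifts have no source.** This also stands; they are assumptions only.

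**Conclusion.** The concern holds in a limited form. Blinding of the data collector is not secured as written, because the article specifies no common dressing for sites that differ by arm, and because it foresees a request that would disclose the arm if made to the caring midwife. It is not shown that the blinding fails, how often the arm would be revealed, or that this would precede the primary measurement.

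The size of any resulting bias is unknown. Under the plan's own SD and 133 per group, an assumed shift of 0.1 to 0.3 cm toward the single injection would move the one-sided type I error from 2.5% to about 5% to 16%. The same shift the other way would lower power from 90% to between 83% and 62%. Since this is a secondary route beside the woman's own unblinded rating, the point is an inexpensive improvement to a safeguard that the plan itself chose.

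**What to change.** 1. **Dressing.** State in Blinding that every woman receives a dressing of the same size in the same position relative to the four standard sites and her most painful point, covering all of them whatever was injected. Mark the most painful point in every woman before the envelope is opened, so that marking cannot depend on the arm.
2. **Requests.** Reconcile Blinding with the text after Figure 4. Word any further request neutrally as one for a repeat injection, directed where feasible to the team leader, who already knows the allocation. What is then given stays as the plan states.

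**Cost.** A larger dressing, one marking step and a change of wording. Directing requests to the team leader touches labour-ward workflow, which is why it should apply only where feasible. Neither change removes the bias that may come from the woman's own knowledge of her allocation.

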### Data collection

Upon randomisation the attending Midwife will document the following data:

• UR number

• Gravity and Parity

• Gestation

• Spontaneous or induced labour

• Findings of last vaginal exam and time

• VAS score and time

• Time of administration

Following administration of SWI the following data will be recorded:

• VAS related to analgesia effect at 10 mins

• VAS related to discomfort felt during the procedure (at 10 mins)

• VAS related to analgesic effect at 30 minute intervals up to 2 hours post procedure

At Site One the following data will be extracted from the obstetric database by the research midwife following birth:

• Age

• Booking weight & BMI

• Mode of birth

• Time of birth

• Any other analgesia used (pharmacological and non pharmacological)

• Model of care

• Educational level

The obstetric databases at Site One and Site Two vary slightly in the data items collected. As separate data collection forms have been generated for the randomisation process for Site Two, the data collection forms have been amended to account for any differences in information captured by the database.

The following self-reported data will be sought from the woman within 48 hours following birth:

• Perceived satisfaction with SWI administration

• Perceived satisfaction with SWI analgesic benefit

• Likelihood to use again with subsequent labour

• Likelihood to recommend to SWI to others

Data will be collected by the Midwife caring for the labouring woman then returned to a securely locked cupboard. Completed data forms will be de-identified and entered into a password protected electronic database. Identified data collection forms will be kept in locked storage for 15 years. Data collection forms at the second site will be stored in a locked cupboard and collected on a fortnightly basis. Data will be entered into a Microsoft Excel spreadsheet and transmitted as a password protected file

